## Methods

### Design

This is a randomized study with 1 year of follow-up. The intervention programs will be offered at Araba University Hospital and biological samples will be analyzed at Complutense University of Madrid.

The randomized clinical trial was registered in 2014 (ClinicalTrials.gov Identifier NCT02319746). This clinical trial fulfills the Standard Protocol Items: Recommendations for Interventional Trials (SPIRIT) Checklist (Additional file 1). The efficacy of a specific treatment program for cannabis abuse (cognitive behavioral treatment + pharmacological treatment) will be compared to that of standard treatment (psychoeducation + pharmacological treatment) in patients with FEP who are cannabis users.

### Participants

FEP patients who are cannabis users and meet the inclusion criteria (listed below) are to be included and randomly assigned to one of the two treatment groups. The sample size calculation was performed using data published in the literature related to the main theme of the study (Bonsack et al., 2011 [31]; Edwards et al., 2006 [32]; Hjorthøj et al., 2012; Madigan et al., 2013 [34]) and using Ene 2.0 software. To achieve a power of 80% to detect differences from the null hypothesis, H0: *μ*1 = *μ*2, using a bilateral Student’s *t* test for two independent samples, with a significance level of 5%, we need to include 30 patients in the experimental group and 30 patients in the control group, meaning a total of 60 patients for the study.

#### Inclusion criteria

The study inclusion criteria for both groups are:Being diagnosed as having had a first psychotic episode: (i.e., schizophrenia, schizophreniform disorder, schizoaffective disorder, delusional disorder, bipolar disorder, atypical psychosis, brief psychotic disorder, or major depressive disorder with psychotic symptoms) according to the revised fourth edition of *Diagnostic and Statistical Manual of Mental Disorders, Fourth Edition, Text Revision* (DSM-IV-TR) [36]Being a regular cannabis user (Table 1):

**Table 1 Tab1:** Classification of cannabis use for selection of participants

Severity of consumption	DSM-IV-TR^a^ criteria for abuse or dependence	Europ-ASI^b^ scores
Dependence	Meet at least minimal DSM-IV-TR criteria for cannabis dependence	8–9
Abuse	Meet ≥1 DSM-IV-TR criteria for cannabis abuse	4–7
Use	Meet DSM-IV-TR criteria for cannabis abuse but not the duration criterion (≥12 months) or ≥12 months of use but do not meet any DSM-IV-TR criteria for cannabis abuse	2–3
No use	No significant symptoms	0–1

^a^Revised Fourth Edition of the Diagnostic and Statistical Manual of Mental Disorders (DSM-IV-TR) [37]

^b^European Addiction Severity Index (Europ-ASI) [37,38]Dependence or abuse of cannabis according to *Diagnostic and Statistical Manual of Mental Disorders, Fourth Edition, Text Revision* (DSM-IV-TR) criteria [36].Dependence or abuse of cannabis according to the scores of the European Addiction Severity Index (EUROP-ASI) [37, 38] (scores of 4 to 7: abuse; scores of 8 to 9: dependence)Aged between 15 and 40 years. In the case of minors (under 18 years of age), written informed consent will be requested from their parents or guardiansBeing in remission from a first psychotic episode (the patients being required to be in remission, without any relapses in a period no more than 5 years from the first psychotic episode)

#### Exclusion criteria

The study exclusion criteria for both groups are:Presenting organic brain pathologyPresenting mental retardation according to DSM-IV-TR criteria

#### Randomization

Patients are to be randomly assigned to one of the two treatment groups by permuted block randomization with a block size of 4 and a 1:1 allocation using a computer-generated random sequence. The allocation sequence will be prepared by an independent person not otherwise involved in the trial.

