### Trial status

Patient recruitment has not been completed at the time of submission.

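### One fixed, printed block size of 4 at a single hospital makes about a third of assignments deducible in advance, if enrolling staff can follow the earlier allocations

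*Protocol article*

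**What the plan says.** The Randomization section of the protocol article specifies "permuted block randomization with a block size of 4 and a 1:1 allocation", drawn from a computer-generated sequence. Its one stated safeguard is this: "The allocation sequence will be prepared by an independent person not otherwise involved in the trial". It mentions neither a varying block size nor stratification factors.

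Three other places bear on the point:
- **Setting.** The Design section states: "The intervention programs will be offered at Araba University Hospital".
- **Visibility of the arms.** Under Intervention programs, the experimental arm receives weekly cognitive behavioral therapy aimed at cannabis cessation and the control arm weekly psychoeducation, each for 16 weeks. Whoever delivers the sessions knows the arm.
- **Timing.** Trial status reports: "Patient recruitment has not been completed at the time of submission".

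The Participants section sets the target: "we need to include 30 patients in the experimental group and 30 patients in the control group, meaning a total of 60 patients". The Procedure section lists informed consent and assessment before random assignment.

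**The concern.** Permuted blocks keep the arms balanced by making later places depend on earlier ones. With one small block size that everyone knows, an observer who has followed the sequence can work out some assignments before they are made. An independent list preparer hides the list, but does not hide what follows from assignments already made. Concealing the next assignment in an envelope or at a central office would not hide it either, because the deduction does not need the envelope.

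What is at stake is selection bias. Someone who knows the next arm can bring a given patient forward or hold the patient back. Patients are eligible while in remission, up to 5 years from the first episode, so enrolment need not be immediate and its timing can be chosen. With 30 patients per arm, a few placements of this kind could affect the comparison, and the planned analyses could not be relied on to remove the effect.

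**Working it through.** **Inputs**
- Block size 4, allocation 1:1 (Randomization). Each block holds two A and two B.
- Total 60 patients (Participants), so 60 / 4 = 15 complete blocks.
- Assumed, not stated: one running sequence without strata, and an observer who knows all earlier assignments in order and where blocks start.

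The article gives no predictability figure, so there is none to reproduce.

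**Share known with certainty.** The six orders AABB, ABAB, ABBA, BAAB, BABA and BBAA are equally likely. An assignment is known once one arm is used up within the block.
- Place 4 is always known.
- Place 3 is known only in AABB and BBAA, 2 of the 6 orders.

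Expected number known per block = (2 × 2 + 4 × 1) / 6 = 8 / 6 = 1.333.

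Share = 1.333 / 4 = 33.3%.

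Over the trial: 15 × 1.333 = 20 of 60. The minimum is 15 × 1 = 15 and the maximum 15 × 2 = 30. The count is 15 + Binomial(15, 1/3), with a central 95% range of 17 to 24.

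**Best-guess accuracy.** The observer always guesses the arm with more places left and tosses a coin when they are equal.
- Place 1: 1/2
- Place 2: 2/3
- Place 3: (1/3) × 1 + (2/3) × (1/2) = 2/3
- Place 4: 1

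Mean = (0.500 + 0.667 + 0.667 + 1.000) / 4 = 70.8%.

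**Alternatives.** The fixed-block rows come from the same enumeration. The mixed-block rows come from simulating 1,500 trials of 60 patients, with an observer who knows the set of sizes (but not which size is in use) and all earlier assignments.

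| Design | Known with certainty | Best guess correct |
|---|---|---|
| Fixed 4 (as planned) | 33.3% | 70.8% |
| Fixed 6, size known | 25% | 68.3% |
| Random mix of 4 and 6 | about 5.5% | about 69% |
| Random mix of 2, 4 and 6 | about 4.1% | about 70% |

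The enumerated figures support the mixed-block accuracies. Expected correct guesses per block are 1.5 for size 2, 2.833 for size 4 and 4.1 for size 6. The mix of 2, 4 and 6 gives (1.5 + 2.833 + 4.1) / 12 = 70.3%, and the mix of 4 and 6 gives (2.833 + 4.1) / 10 = 69.3%.

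The mixed-block figures are for a full sequence of 60. The number of patients still to be enrolled is not stated; repeating the simulation for shorter sequences gave certainty shares of the same order.

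**Imbalance.** A sequence that stops inside a block of size b is out of balance by at most b / 2, so by 6 / 2 = 3 patients with sizes up to 6. The present design ends exactly balanced at 60.

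**The case against.** Fixed blocks of 4 are a valid design and contradict nothing in the article. The one-third figure needs a person who enrols patients, knows every earlier assignment in order and knows where blocks start. The article does not say who recruits, or that recruiters share what therapists know. It shows only that those delivering the sessions know the arm. All this stands, and it is why the finding is conditional. One hospital and visibly different therapies make the condition plausible, not established.

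The article is also silent on strata. Silence in a condensed article does not show that there are none, so a single sequence is an assumption. How each assignment is released may be described in the full protocol and is not criticised here. Structured diagnostic and severity criteria limit discretion over who qualifies, but not over when a patient is enrolled.

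Some stronger readings are tempting, but the documents do not support them:
- **That the block size was published while recruitment was open.** Trial status speaks only of the time of submission. Open recruitment at publication is an inference.
- **That 71% correct guessing should be set against 50%.** The 50% belongs to unrestricted randomization. Any blocked design with small blocks exceeds it, and the remedy below leaves the rate at about 69–70%.
- **That the cessation outcome depends strongly on motivation, so steering would have a large effect.** The Background says only that first-episode patients show greater motivation for change than chronic patients. The size of any bias cannot be derived from the article.
- **That predictability threatens the single-blind assessment.** An assessor could infer an arm from block position only by already knowing other patients' assignments, and would then be unblinded regardless of block size.

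**Conclusion.** The point holds in a limited form. The article fixes and prints one small block size in a setting where earlier allocations are easy to observe. On average 33% of assignments, about 20 of 60 and between 15 and 30, can then be deduced with certainty before enrolment. This rests on two assumptions that the article neither states nor excludes: that enrolling staff know the earlier assignments in order and the block starts, and that there is one unstratified sequence. The independent preparation of the list does not remove the exposure.

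A reader might infer that allocation was in fact steered. Nothing in the article supports that; the arithmetic shows opportunity only. It is an avoidable weakness in a stated design choice, and worth correcting because the correction is cheap. The count of 20 applies to the whole trial. How many assignments a change could still protect depends on the number of patients left to enrol, which is not given.

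**What to change.** For the patients still to be enrolled, starting at the next block boundary, have the independent person generate a new list with randomly varying block sizes, for example 4 and 6, or 2, 4 and 6. Keep the sizes and the list from site staff. Record the date and the sequence number at which the new list takes over.

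The gain is in removing certainty: from 33.3% to about 4–6%, even if staff learn which sizes are in the mix. Best-guess accuracy hardly moves. Of the two mixes, 2, 4 and 6 leaves slightly fewer certain assignments, while 4 and 6 gives slightly lower guessing accuracy; either is acceptable.

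The Procedure section already lists consent and assessment ahead of assignment, so it is enough to confirm that each assignment is released only after both are recorded.

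The cost is one new computer-generated list and a possible final imbalance of at most 3 patients. If recruitment has closed, the list can no longer be changed, and the fixed block size should be reported as a limitation together with what enrolling staff knew of earlier assignments.

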### Assessment

Data collection is to be based on an assessment protocol for gathering data on sociodemographic, clinical and cannabis/other substance use-related variables. All patients are to be assessed at baseline, post-treatment and in the follow-up period (at 3 and 6 months and 1 year of follow-up from the end of the treatment program) (Table 2).

**Table 2 Tab2:** Assessment protocol

Assessments	Pre-treatment	Post-treatment	Follow-up^a^		
Sociodemographic variables	X				
Cannabis/other substance use-related variables					
Use	X	X	X	X	X
Severity	X	X	X	X	X
Clinical variables					
Diagnosis	X	X	X	X	X
Clinical severity	X	X	X	X	X
Illness awareness	X	X	X	X	X
Medication adherence	X	X	X	X	X
Clinical symptomatology	X	X	X	X	X
Psychosocial functioning	X	X	X	X	X
Biological variables					
Peripheral blood mononuclear cells	X	X	X	X	X
Toxins in urine	X	X	X	X	X

^a^Follow-up: 3 and 6 months and 1 year of follow-up from the end of the intervention program

#### Sociodemographic variables

Data on sociodemographic variables (age, gender, educational level, socioeconomic level, employment status, family history of psychiatric disorders) are to be collected at baseline.

#### Cannabis/other substance use-related variables

*Variables related to cannabis/other substance use* include frequency of use, dose, age of onset of use and history of use (years)*Severity of cannabis/other substance use* is assessed with the EUROP-ASI [37, 38] and the Cannabis Use Problems Identification Test (CUPIT) [39]

The EUROP-ASI, an adaptation of the Addiction Severity Index (fifth version), is a structured interview for clinical practice and research. It is designed to assess severity of the substance use problem and makes it possible to monitor and quantify changes in problems commonly associated with substance abuse. Translated into practically all European languages, the reliability and validity of EUROP-ASI are well established [40–44] and it has been shown to have high internal consistency (Cronbach’s alpha coefficient >0.70) [41, 42, 44, 45] and moderate-excellent interrater reliability (interclass correlation coefficient 0.62–0.99) [43, 44].

CUPIT is a brief self-report screening instrument for the detection of currently and potentially problematic cannabis use. It is composed of 16 items and has demonstrated good test-retest (0.88 to 0.99) and internal consistency reliabilities for the two derived subscales, “dependence” (0.92, whole sample) and “problems” (0.90 adults, 0.79 adolescents), and it has reliably discriminated diagnostic subgroups (no diagnosis, abuse/harmful use, dependence) across the problem severity continuum (diagnostic utility) [39].

#### Clinical variables

DiagnosisPatients are diagnosed according to the DSM-IV-TR criteria using the Structured Clinical Interview for the Diagnostic and Statistical Manual of Mental Disorders, Axis I Disorders (SCID-I) [45]. This interview is to be carried out independently but at the same time by two experienced clinicians, to confirm inter-rater reliability in the diagnosis of patientsClinical severityThe Clinical Global Impression Scale (CGI) [46] is used to assess symptom severity, global improvement and therapeutic response. It is a 3-item observer-rated scale. Items 1 and 2 are rated on a seven-point scale; and item 3 is rated on a five-point scale, from 0 to 4 (taking into account therapeutic efficacy and treatment-related adverse events)Illness awarenessThe illness awareness of patients is measured using the Scale to assess Unawareness in Mental Disorders (SUMD) [47, 48]. This scale explores the thoughts and beliefs of patients regarding their illness and its pharmacological treatmentMedication adherenceThe type of pharmacological treatment is recorded and medication adherence is estimated with the 4-item Morisky Medication Adherence Scale [49, 50]. It assesses attitudes of patients towards their treatment. Patients with a score of 4 were considered to have good adherence, while those with a score between 0 and 3 were classified as having poor adherenceClinical symptomatologyPsychotic symptoms are measured using Positive and Negative Syndrome Scale (PANSS) [51, 52]. The PANSS is a relatively brief interview used for measuring positive, negative and general symptoms of patients with schizophrenia. The ratings provide summary scores on a 7-item positive scale, a 7-item negative scale and a 16-item general psychopathology scale.Depressive symptoms are measured with the Hamilton Depression Rating Scale (HDRS-21) [53, 54]. This is a 21-item scale that assesses the severity of depressive symptoms (range: 0–52)Manic symptoms are measured using the Young Mania Rating Scale (YMRS) [55, 56]. This is an 11-item scale used to assess the severity of manic symptoms (range: 0–60).Anxiety symptoms are measured using the Hamilton Anxiety Scale (HAM-A) [57, 58]. This has been developed to measure the severity of anxiety symptoms, both psychic anxiety (mental agitation and psychological distress) and somatic anxiety (physical complaints related to anxiety)Psychosocial functioningThe functioning of patients is measured using the Functioning Assessment Short Test (FAST) [59]. The FAST is a brief instrument designed to assess functional impairment in severe mental disorders. The 24 items of the scale cover six specific areas of functioning: autonomy, occupational functioning, cognitive functioning, financial issues, interpersonal relationships and leisure time

#### Biological variables

To assess whether the treatment program is able to normalize any changes in the components of the ECS, peripheral blood mononuclear cells (10 ml of venous blood anticoagulated with ethylenediaminetetraacetic acid (EDTA)) are to be collected at baseline, at post-treatment and at 3 and 6 months and 1 year of follow-up. In peripheral blood mononuclear cells, the following elements of the endogenous cannabinoid system are to be measured: synthesis enzymes (NAPE-PLD, DAG-L), degrading enzymes (FAAH, MAG-L), and receptors (CB1 and CB2) by Western blot (protein) and reverse transcription-polymerase chain reaction (mRNA).

Toxins in urine are assessed with an immunochromatographic test to detect drug metabolites at baseline, at sessions 4 and 8 of the psychological treatment, post-treatment, and at 3 and 6 months and 1 year of follow-up.

#### Procedure

Patients will be assessed after being informed of the objectives of the study and giving their informed consent to participate. All participants will be evaluated individually and will be randomly assigned to one of two treatment groups. Data will be collected following an assessment protocol (see “Assessment” section) that will be implemented at baseline, post-treatment and in the follow-up period (at 3 and 6 months and 1 year of follow-up from the end of the intervention program) (Fig. 1).

**Fig. 1 Fig1:**
[figure not shown]
Study procedure

#### Statistical analysis

IBM SPSS version 23 will be used for the statistical analysis. The sociodemographic characteristics of the patients will be analyzed using descriptive statistics. Differences between the two intervention groups (cognitive behavioral therapy versus psychoeducation) will be analyzed using the χ^2^ test (or Fisher’s test where *n* ≤5) for categorical variables and the Student’s *t* test or Mann-Whitney *U* test (depending on the distribution of the data) for continuous variables.

The differences in cannabis use reduction between two intervention groups will be analyzed using Student’s *t* test and/or the Mann-Whitney *U* test and mixed models. Effect sizes will be calculated for differences in cannabis abstinence based on Cohen’s *d* or *r* [60] for Student’s *t* test and the Mann-Whitney *U* test, respectively. The results will be interpreted as small if *d* values are between .2 and .49, medium if *d* values are between .5 and .79, and large if *d* values are higher than .8.

Differences in efficacy between the interventions in terms of clinical and functional outcomes of patients will be analyzed with repeated measures models (baseline, post-treatment, 3 and 6 months and 1 year of follow-up) and logistic regressions.

Furthermore, whether cannabis abstinence is associated with better clinical and functional outcomes will be analyzed using linear regression models for continuous dependent variables, and Poisson regression models for categorical dependent variables.

Finally, the biological data of patients will be studied in conjunction with clinical data using multivariate analyses. Specifically, the possible alterations in the components of the ECS and the influence of the specific cognitive behavioral therapy program for cannabis cessation on the normalization of ECS will be analyzed using repeated measures models, mixed models or analysis of covariance. Further, the relation between normalization of elements of the ECS and improvement in symptoms and psychosocial functioning, attributable to the specific treatment, will be assessed by regression models.

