**Methods/design:**

This is a single-blind randomized study with 1 year of follow-up. Patients are to be randomly assigned to one of two treatments: (1) specific cognitive behavioral therapy for cannabis cessation composed of 1-hour sessions once a week for 16 weeks, in addition to pharmacological treatment scheduled by the psychiatrist, or (2) a control group (psychoeducation + pharmacological treatment) following the same format as the experimental group. Participants in both groups will be evaluated at baseline (pre-treatment), at 16 weeks (post-treatment), and at 3 and 6 months and 1 year of follow-up. The primary outcome will be that patients in the experimental group will have greater cannabis cessation than patients in the control group at post-treatment. The secondary outcome will be that the experimental group will have better clinical and functional outcomes than the control group.

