The main aim of this article is to describe the design of a randomized controlled trial focused on comparing the efficacy of a specific cognitive behavioral therapy program for cannabis cessation with standard treatment in patients with FEP who are cannabis users. The study design, assessment and intervention program are described.

The specific objectives of the study are:To assess whether a specific cognitive behavioral therapy program for cannabis cessation is associated with a greater reduction in use of cannabis than standard treatmentTo assess whether this type of program for cannabis cessation is associated with better outcomes of the psychotic disorder (i.e., reduction in symptoms and improvement in psychosocial functioning) in the follow-up than standard treatmentTo analyze the relation between cannabis abstinence and clinical and functional outcomes of patientsTo determine whether there are systemic alterations in the components of the ECS and, if so, whether a specific cognitive behavioral therapy program for cannabis cessation is able to normalize such alterationsTo assess whether normalization of elements of the ECS is directly related to reductions in symptoms and improvements in psychosocial functioning attributable to the proposed specific treatment

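### The declared primary outcome is cannabis cessation, but the first objective, the sample size and the cannabis analysis concern use reduction or means, and no single deciding test is named

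*Protocol article*

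**What the plan says.** The protocol article describes its main question in five places.

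- **Abstract, Methods/design:** the primary outcome is that "patients in the experimental group will have greater cannabis cessation than patients in the control group at post-treatment".
- **Background, first specific objective:** whether the programme "is associated with a greater reduction in use of cannabis than standard" treatment.
- **Participants:** 30 patients per arm, from a two-sided 5% Student's t test of equal means with 80% power. No mean difference, SD or cessation rate is given.
- **Statistical analysis, cannabis paragraph:** "The differences in cannabis use reduction between two intervention groups will be analyzed using Student’s *t* test and/or the Mann-Whitney *U* test", and also by mixed models. The next sentence reads "Effect sizes will be calculated for differences in cannabis abstinence", using Cohen's d or r.
- **Statistical analysis, first paragraph:** after the description of sociodemographic characteristics, a general sentence says that differences between the two arms "will be analyzed using the χ^2^ test (or Fisher’s test where *n* ≤5) for categorical variables", and by t test or Mann-Whitney, depending on the distribution, for continuous ones. It does not mention cessation.

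Logistic regression appears only for clinical and functional outcomes.

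**The concern.** Cessation and reduction are different quantities. A programme can halve consumption while nobody stops, or get a few patients to stop while the mean barely moves. The article fixes one as the primary outcome and the other as the thing analysed. Followed as written, the trial could find a difference in reduction and present it as the declared result on cessation.

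Two features add to this. The wording for the cannabis comparison permits two tests and a family of models without saying which one decides. And d and r describe differences in means or ranks, so they are not the natural effect measures for the proportion of patients who are abstinent.

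**Working it through.** **1. What each part of the text implies**

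| Place | Quantity | Scale |
|---|---|---|
| Abstract, primary outcome | cessation at post-treatment | yes/no |
| First specific objective | reduction in use | amount |
| Sample size | difference in means | continuous |
| Cannabis analysis | reduction in use | continuous or ranked |
| Effect size sentence | abstinence, by d or r | yes/no state, continuous measure |

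The objective, the sizing and the test fit one another. The declared primary outcome does not fit them, and the effect-size sentence mixes the two.

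**2. The stated sample size**

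It cannot be reproduced forwards without a mean difference and SD. Solving backwards by the normal approximation:

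d = (1.960 + 0.842) × √(2/30) = 2.802 × 0.2582 = 0.723

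The exact t test gives 0.736. So 30 per arm is a possible figure for means, at a standardised difference of about 0.74. It says nothing about cessation.

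**3. What 30 per arm gives for cessation**

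Power = Φ[(|p1 − p2| − 1.96 × se0) / se1], where se0 = √(p̄(1 − p̄) × 2/30), p̄ is the mean of p1 and p2, and se1 = √([p1(1 − p1) + p2(1 − p2)]/30). The control rates are assumptions, since the article gives none.

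- 10% v 30%: se0 = 0.1033, se1 = 0.1000. Power = Φ[(0.20 − 0.2024)/0.1000] = Φ(−0.024) = 49%.
- 40% v 60%: se0 = 0.1291, se1 = 0.1265. Power = Φ[(0.20 − 0.2530)/0.1265] = Φ(−0.419) = 34%.

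| Assumed control rate | Power, 20-point difference | n per arm for 80% |
|---|---|---|
| 10% | 49% | 62 |
| 20% | 39% | 82 |
| 30% | 35% | 93 |
| 40% | 34% | 97 |
| 50% | 35% | 93 |

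For a 30-point difference, power is 65–78% and 80% needs 32–42 per arm.

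**4. False positives if the best of the permitted tests is reported**

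Simulation with no true effect, 30 per arm, nominal two-sided 5%, and an assumed within-patient correlation of 0.5. The first three rows use 10,000 trials each, with a t test on mean change over all follow-up visits standing in for the mixed model. The last row uses 4,000 trials, with a baseline-adjusted model standing in.

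| Assumed distribution of use | Better of t and Mann-Whitney | Model added |
|---|---|---|
| Normal | 6.5% | 9.0% |
| Log-normal | 6.4% | 8.7% |
| Days of use, 30% zeros after baseline | 6.1% | 9.1% |
| Log-normal, 25% zeros | about 6.5% | 8.4% |

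If the test is instead chosen by a distribution check (a Shapiro test, assumed), the log-normal setting with 25% zeros gives 4.7%, so there is no inflation.

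**The case against.** Four arguments can be made for the plan.

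- **A test for proportions is present.** The general chi-square/Fisher sentence names the two treatment arms and is not limited to baseline variables, so a yes/no abstinence variable can fall under it. This stands. A reader might infer that cessation would never be tested, but the text does not support that. What it supports is that no test is tied to the primary outcome and that nothing ranks such a test against the reduction analysis.
- **There is a rule for t test or Mann-Whitney.** The general sentence chooses by distribution, which need not inflate the error rate. This stands in part. The rule has no criterion, and the cannabis sentence replaces it with wording that allows both tests.
- **Detail belongs in the analysis plan.** The instrument, the abstinence window and the model specification may well be settled there. The disagreement between outcome, objective, sizing and test is in the article itself.
- **Cessation may simply be a loose label.** Since the objective, sizing and test agree with one another, correcting the Abstract would be an equally valid repair. This stands, and the fix allows for it.

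A reader might also infer error rates of 20–30%, because frequency, dose, EUROP-ASI, CUPIT and urine results are all collected. Such figures require a free choice among three to five interchangeable measures at an assumed correlation of 0.5. The article lists assessments but does not say that any of them may be declared primary, and the urine test detects metabolites rather than giving a score.

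**Conclusion.** The point holds. The article contradicts itself on the quantity that decides the trial, and it leaves the deciding test open. The mismatch of quantity can be read directly from the text and needs no assumptions.

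The error-rate part is modest: about 6–6.5% if the better of t test and Mann-Whitney is taken, and about 8–9% with a model added. These figures rest on the assumed distributions, the correlation of 0.5 and a best-of-several reading of the wording.

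The consequence for sample size is larger. The 80% power statement applies to a difference in means. If cessation is primary, 30 per arm gives about 34–49% power for a 20-point difference over assumed control rates of 10–50%.

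**What to change.** Decide which quantity is primary, and make outcome, test, effect measure and sample size agree before any comparison by arm is seen. Recruitment was not complete at submission.

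**If cessation stays primary:**
- Define abstinence at the 16-week assessment from the use report and urine test already collected, and state how patients with missing results are counted. The lowest EUROP-ASI band in Table 1 should not serve as the cut-off by itself: it is a severity band given for selecting participants.
- Name one test of the proportion abstinent, for example chi-square/Fisher, or logistic regression adjusted for baseline severity.
- Report a risk difference with 95% CI in place of d or r.
- Make use reduction secondary, with one named measure and one model, and delete the and/or wording.
- Restate the power for cessation with its assumed rates.

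**If reduction is the intended primary:** change the Abstract to say so, name one measure and one test, and do not report the result as cessation.

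Either route needs only wording and no new data. The first has a real cost: the means-based sample size no longer supports the 80% claim, so the trial must either accept and state lower power or recruit more patients (62–97 per arm for 80% power at a 20-point difference, under the same assumed rates). The second keeps the sizing basis but gives up the claim about cessation.
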